### Sample size and sampling technique

Overall, 120 patients with T1D will be randomized into four equal groups for evaluating changes in HbA1C using multiple measurements at multiple time points. Thirty patients in each group will be required in order to achieve 80% power for a two-sided level of significance of 5%, using a standard deviation of change in HbA1c between 1.1% and 2.3% and absolute difference of at least 2% expected over a period of 6 months within a group from baseline as well as when compared across the four groups [29]. A consecutive sampling technique will be used to enroll participants visiting AKU pediatric and endocrinology clinics and fulfilling the eligibility criteria.

### Interventions

A predesigned log book file will be provided to all patients in all groups to keep their records of daily blood sugar measurement and insulin therapy (Fig. 2). Random allocation of patients to one of the four groups will be done through support from the CTU at AKU using sealed envelopes. The first intervention group will receive an e-device for daily step count (fit bit). The other two intervention groups will receive reminder mobile e-messages: one will receive only mobile messages (without fit bit) about maintaining the log book for blood glucose and the other will receive the mobile messages for maintaining the log book for blood glucose and for fit bit along with an e-device for measuring step count (Table 1). Fit bit has been shown to have high validity and reliability [10], with the potential advantage over other similar e-devices (accelerometers, pedometers, or actigraphs) of increasing the sustainability of this intervention given that it is cost-effective [27].

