## Methods/design

### Study design

A factorial design will help to study lifestyle changes for self-management of T1D (Fig. 1). A randomized controlled method will enroll patients in a predefined sequence, assigning them in four groups. All groups will be working with a newly designed standard log book for documenting records for blood sugar and routine insulin dosage and care as provided by doctors, nurses, and nutritionists. The first group will all receive routine care follow-up, the second group will receive an additional e-device for measuring step count (fit bit), the third group will receive routine care and e-messages as reminders to maintain a daily log book, and the fourth group will receive an e-device for measuring step count (fit bit) and e-messages about maintaining the log book, blood glucose levels, and step count in addition to routine care. All groups will be followed up overall for a period of 6 months. HbA1c as a main outcome will be measured at least three times, at baseline, and then once every 3 months.

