### Randomization

Unique allocation numbers will be designated by the Clinical Trail Unit (CTU) with computer-generated block randomization, using a block size of four. Sealed opaque identical envelopes will be received by the principal investigator (PI) from the CTU in an order that will be followed to enroll study participants in all four groups. The data collector will be instructed to assign allocated numbers to participants in sequential order as they are enrolled. Upon opening the envelope, the group, A, B, C, and D, will be revealed to the data collector and items related to the appropriate group will be explained to the study participant. Group A will be told to follow routine care, group B will receive an additional e-device for measuring step count (fit bit) and the data collector will download the associated application onto the participant’s cell phone, group C will receive routine care and e-message reminders from the data collector to maintain a daily log book, and group D will receive routine care as well as an e-device for measuring step count (fit bit) together with the associated application (downloaded onto the participant’s cell phone by the data collector) and e-messages from the data collector as reminders to maintain their log book, blood glucose levels, and step count.

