**Fig. 2 Fig2:**
[figure not shown]
Logbooks for groups A and C to record their daily blood sugar readings and insulin doses and for groups B and D to record daily blood sugar readings, insulin doses, and step count

**Table 1 Tab1:** Mobile messages by group

E-MESSEGES FOR GROUP C	E-MESSEGES FOR GROUP D
Remember to check your blood sugars before every meal and record it in your logbook. Keep up the good work.	How many steps have you taken today? Make sure your fitbit is charged to record all that hard work! Good luck and have a healthy day
Don’t forget to check and record your blood sugar and insulin dose in your logbook. This record will help you to discuss it with your doctor and make your sugar levels near to the targets. Have a good day!	Recording your step count can help you to manage your blood sugar, so Fitbit is here to help you to count your steps daily. Don’t forget to charge it. Have a good day!
Keeping an eye on your blood sugar. Knowing this can help you and your doctor to adjust your food choices and insulin doses accordingly. Thanks for checking and recording it in your log book!	Remember! Any type of physical activity you do will help you lower your blood glucose! It’s time to go for a walk and increase your daily steps. Fitbit is here to count your every step so don’t forget to note your steps daily in your logbook. Thank you for all your hard work!
Self-testing of your blood sugar is an important tool in managing your treatment plan and preventing diabetes complications, so try to keep your blood sugar levels record in your logbook as suggested by your physician and help yourself and your doctor to manage your treatment accordingly.	Fitbit is with you to count your steps during housework, outdoor work, job activities, recreational activities, and exercise. So charge you fitbit as required and don’t forget to record your steps daily in logbook. Thanks
Self-monitoring of blood sugar levels provides useful information for diabetes management as it can help you reach your overall treatment goals. So keep checking and recording it in your logbook. Good day!	Improved fitness lowers your blood glucose level, relieves stress, helps insulin work better and strengthens the heart, muscles, and bones. It’s time to set your goals and make your life healthier. Wear your fitbit device all the day and record your steps in log book. Don’t forget to charge it. Stay Healthy!

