It is time to check your blood sugar levels and don’t forget to keep recording of your sugar levels and insulin dose in you logbook. Thanks for your all efforts.	If you sit for long hours at work or at home, try to get up once every hour and take a quick walk around the room. Walking is a great way to get fit! So use your fitbit and record all the steps you have taken in the log book. Thanks you for your Hard work!

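### The text says group D is reminded about glucose logging and steps, but no group D message in Table 1 asks for a glucose check or entry; if that column is complete, messages are a different intervention in C and D

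*Protocol article*

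**What the plan says.** The running text is consistent about group D:

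- Study design: "e-messages about maintaining the log book, blood glucose levels, and step count in addition to routine care".
- Randomization: "e-messages from the data collector as reminders to maintain their log book, blood glucose levels, and step count".
- Interventions, in the sentence that cites Table 1: "the other will receive the mobile messages for maintaining the log book for blood glucose and for fit bit".

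The same Interventions sentence describes group C: "one will receive only mobile messages (without fit bit) about maintaining the log book for blood glucose". Read together, these passages give group D the group C content with step-count prompts added.

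Table 1 sets out the messages in two columns, one for group C and one for group D, with six messages in each. The group C column opens with "Remember to check your blood sugars before every meal and record it in your logbook". The group D column opens with "How many steps have you taken today? Make sure your fitbit is charged to record all that hard work". Later group D entries include "Wear your fitbit device all the day and record your steps in log book" and "So use your fitbit and record all the steps you have taken in the log book".

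The design is called factorial in Study purpose, Study design and Outcome measures. The first primary objective is the effect on HbA1c of messages about log books and glucose self-monitoring, against routine care. Outcome measures plans to explore interactions between the groups over time. The Discussion expects an interactive effect of e-message reminders and step count on blood glucose.

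**The concern.** A factorial reading of four arms requires each factor to mean the same thing at both levels of the other. Here the message factor is present in C (without device) and in D (with device). On the running text, the glucose log-book reminder is in both. On Table 1 as printed, C is prompted to measure and record glucose, and D is prompted to walk, charge the device and record steps.

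The contradiction concerns what a randomized arm receives, so the analysis cannot repair it. Follow-up and other procedures has trained staff sending messages daily to the assigned groups. If they work from Table 1, group D never gets the reminder that the first primary objective is about. Two quantities would lose their meaning: any message effect that combines C and D, and the interaction that the authors expect.

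**Working it through.** **1. Message content in Table 1, counted by column.**

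| | Group C | Group D |
|---|---|---|
| Messages listed | 6 | 6 |
| Concern checking or recording blood sugar | 6 | 0 |
| Concern steps, fit bit or activity | 0 | 6 |
| Mention blood sugar or glucose at all | 6 | 3 |
| Mention the log book | 6 | 4 |

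The last two rows explain why the group D column can look closer to the text than it is. In the three group D messages that name blood sugar or glucose (second, third and fifth), it appears only as something that activity or step recording improves. In the four that name the log book (third to sixth), the entry requested is steps. None asks for an insulin entry.

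**2. What each contrast measures under the two readings.** Write A, B, C and D for the mean HbA1c change in each group, G for the effect of the glucose-log messages and S for the effect of the step messages. For simplicity, assume that effects add and that there is no true interaction with the device.

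- C − A = G under either reading.
- If group D receives both sets: D − B = G + S. The pooled effect ½[(C − A) + (D − B)] = G + S/2, and the interaction (D − B) − (C − A) = S.
- If group D receives only the Table 1 column: D − B = S. The pooled effect = (G + S)/2, and the interaction = S − G.

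In the second case the interaction contrast is non-zero whenever S differs from G, even when the device does not change the effect of any message. The pooled effect is then an average of two different interventions. As an illustration on an assumption the documents do not make: if G were the planned 2 points and S were 0, the pooled effect would be (2 + 0)/2 = 1 point.

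**3. Is C v A still adequate?** Inputs from Sample size and sampling technique: 30 per group, 80% power, two-sided 5%, difference 2 points, standard deviation of change 1.1 to 2.3.

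The plan's own figure first: n per group = 2 × [SD × (1.960 + 0.842) / 2]².

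- SD 2.3: 2 × (2.3 × 2.802 / 2)² = 20.8, so 21 per group.
- SD 1.1: 2 × (1.1 × 2.802 / 2)² = 4.7, so 5 per group.

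The stated 30 is not reproduced by this formula, but it errs on the large side, and that does not affect the present point.

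Power of C v A with 30 per group at SD 2.3:

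- Standard error = 2.3 × √(2/30) = 0.594.
- 2 / 0.594 = 3.37, and 3.37 − 1.96 = 1.41, giving 92% by the normal approximation. The noncentral t with 58 degrees of freedom gives 91%.
- Difference detectable with 80% power: 2.802 × 0.594 = 1.66 points (1.69 by noncentral t), below the planned 2.

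At SD 1.7 and 1.1 the power is above 99%.

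**The case against.** The best defence is that three sections agree on what group D receives, and Interventions cites Table 1 in the very sentence that says so. The group D column may list only the extra, device-specific texts sent on top of the group C set. Nothing says that the column is exhaustive, and this is a condensed article. That reading is possible, and it is why the consequence has to be stated conditionally. But the table assigns messages by group under two separate headings, and nothing in it says that D also receives the C column. The contradiction stands until the authors resolve it.

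A second defence is that even the text gives D more than C, so some difference in content is a declared design choice. This is correct. As step 2 of the working shows, the interaction then also carries the effect of the step prompts. The glucose reminder would nevertheless be common to both message arms, which is what a factorial reading of the first objective needs.

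Two stronger readings are tempting, and the documents do not support them.

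- A reader might infer that the message effect cannot be estimated. It can: C v A is randomized and does not depend on what D receives. The pooled contrast can also be computed. What is in doubt is its interpretation.
- A reader might infer that the trial loses half its sample for the first objective. The protocol states no pooled C+D v A+B contrast. It sizes the trial at 30 per group for a 2-point difference, and Outcome measures already compares each group with routine care. There is no planned 60 v 60 comparison to lose.

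**Conclusion.** The contradiction between the text and Table 1 is established: three sections promise group D reminders about glucose as well as steps, and 0 of 6 listed group D messages contain one, against 6 of 6 for group C.

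The consequence is conditional on the group D column being the complete list. If it is, a pooled message effect has no clear meaning as a single factor, and the expected message-by-device interaction cannot be separated from message content. Group C v group A remains a valid contrast for the first primary objective. Its power is about 91% at SD 2.3 and higher at smaller standard deviations, taking the protocol's 2-point difference as given and assuming complete data on 30 patients per group with no multiplicity adjustment.

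**What to change.** Reconcile Table 1 with Study design, Randomization and Interventions by stating whether group D also receives the group C glucose log-book messages.

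- **If it does:** correct Table 1 and the daily message list used by staff so that the group D entry shows both sets, and note that the step prompts are additional content specific to D.
- **If it does not:** correct the three text sections. Name C v A as the contrast for the first primary objective, and report D v B separately as step messages added to the device. Do not report a pooled message effect, and do not interpret the interaction as one between messages and device.

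The cost is small: a clarifying sentence, a corrected table or text and, if needed, a corrected sending list, using messages already written. The one drawback is that recruitment began in October 2018, so patients may receive different content before and after a correction. The content sent to each patient should therefore be recorded by date.

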**Fig. 2 Fig2:**
[figure not shown]
Logbooks for groups A and C to record their daily blood sugar readings and insulin doses and for groups B and D to record daily blood sugar readings, insulin doses, and step count

**Table 1 Tab1:** Mobile messages by group

E-MESSEGES FOR GROUP C	E-MESSEGES FOR GROUP D
Remember to check your blood sugars before every meal and record it in your logbook. Keep up the good work.	How many steps have you taken today? Make sure your fitbit is charged to record all that hard work! Good luck and have a healthy day
Don’t forget to check and record your blood sugar and insulin dose in your logbook. This record will help you to discuss it with your doctor and make your sugar levels near to the targets. Have a good day!	Recording your step count can help you to manage your blood sugar, so Fitbit is here to help you to count your steps daily. Don’t forget to charge it. Have a good day!
Keeping an eye on your blood sugar. Knowing this can help you and your doctor to adjust your food choices and insulin doses accordingly. Thanks for checking and recording it in your log book!	Remember! Any type of physical activity you do will help you lower your blood glucose! It’s time to go for a walk and increase your daily steps. Fitbit is here to count your every step so don’t forget to note your steps daily in your logbook. Thank you for all your hard work!
Self-testing of your blood sugar is an important tool in managing your treatment plan and preventing diabetes complications, so try to keep your blood sugar levels record in your logbook as suggested by your physician and help yourself and your doctor to manage your treatment accordingly.	Fitbit is with you to count your steps during housework, outdoor work, job activities, recreational activities, and exercise. So charge you fitbit as required and don’t forget to record your steps daily in logbook. Thanks
Self-monitoring of blood sugar levels provides useful information for diabetes management as it can help you reach your overall treatment goals. So keep checking and recording it in your logbook. Good day!	Improved fitness lowers your blood glucose level, relieves stress, helps insulin work better and strengthens the heart, muscles, and bones. It’s time to set your goals and make your life healthier. Wear your fitbit device all the day and record your steps in log book. Don’t forget to charge it. Stay Healthy!
It is time to check your blood sugar levels and don’t forget to keep recording of your sugar levels and insulin dose in you logbook. Thanks for your all efforts.	If you sit for long hours at work or at home, try to get up once every hour and take a quick walk around the room. Walking is a great way to get fit! So use your fitbit and record all the steps you have taken in the log book. Thanks you for your Hard work!

### Follow-up and other procedures

An orientation meeting of endocrinology unit clinicians and their staff will be conducted prior to initiation of the study to obtain their cooperation for sharing their clinics’ schedules a day prior. HbA1c levels will be laboratory measured at least three times, at baseline and then once every 3 months. Every 3 months, 24-hour dietary recall and physical activity assessments will be performed. Patients’ routine clinic visits are at 3 months and follow up visits will be coordinated accordingly for mid and final data collection and 3-monthly HbA1c testing. Instructions for the e-device (fit bit) will be provided to patients in the respective groups, and its use will be demonstrated to them. A written instruction sheet will be placed in the log book for maintaining the blood glucose and insulin records; also, separate instructions will be given to the e-device (fit bit) groups about charging the device daily at night and wearing it during the day. Study participants/parents will be sent e-messages as reminders for maintaining log books and/or step count. Mobile messages will be sent by trained staff on a daily basis to the assigned groups of patients. Log book data will be obtained every 3 months during doctor visits or through e-messages.

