**Methods/design:**

A randomized controlled trial will enroll participants aged 15 years and above in four groups. Each group of 30 participants will be working with a newly designed standard log book for documenting their blood glucose. The first group will be entirely on routine clinical care, the second group will be on routine care and will receive an additional e-device for recording step count (fit bit), the third group will receive routine care and daily motivational e-messages to maintain the log book, and the fourth group along with routine care will receive an e-device for measuring step count (fit bit) and e-messages about maintaining the log book. Patients will be enrolled from pediatric and endocrine clinics of a tertiary care hospital in Karachi. All groups will be followed up for a period of 6 months to evaluate outcomes. Log book data will be obtained every 3 months electronically or during a patient’s clinic visit. HbA1c as a main outcome will be measured at baseline and will be evaluated twice every 3 months. A baseline questionnaire will determine the socio-demographic, nutritional, and physical activity profile of patients. Clinical information for T1D and other co-morbidities for age of onset, duration, complications, hospitalizations, habits for managing T1D, and other lifestyle characteristics will be ascertained. Behavioral modifications for maintaining daily log books as a routine, following e-messages alone, fit bit alone, or e-messages plus using fit bit will be assessed for changes in HbA1c using a generalized estimated equation.

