### Rationale

Adequate glycemic control along with a healthy lifestyle are associated with improved health outcomes and lower morbidity and premature mortality in diabetes patients. Therapeutic insulin regimens need to be strongly regulated during the adolescent period to prevent complications in T1D patients [17]. Adolescents with poor glycemic control had greater proportions of diabetic retinopathy and micro- and macro-albuminuria than patients who maintained their HbA1c levels in a strict therapeutic range [17]. Adherence to management protocols and insulin regimens had an inverse association with occurrence of acute complications in several studies on T1D patients [18, 19]. Poor compliance with or no insulin regimen were directly associated with severity of diabetic ketoacidosis in T1D patients in Pakistan, who needed longer hospital stays [20]. Family-centered care empowering family members to maintain a blood glucose level record sheet, insulin dosage recording, physical activity, and a meal plan resulted in significant differences in behavior and supervision of adolescents with T1D [21]. At the regional level management of T1D is a big challenge as physicians tend not to adhere to the international treatment guidelines regularly [4, 9]. Several e-devices are available to monitor physical activities and these have been studied globally for use by diabetic patients [6, 9–11]. Most of the studies using and e-device for improving patient outcomes have been performed on T2D patients due to its high prevalence [22–27]. T1D patients are usually in the pediatric age bracket and have increased chances of severe acute complications; therefore, multifaceted approaches involving patients, parents, families, doctors, and stakeholders are required for optimal T1D management [12, 13, 17, 20, 28]. A study done in India assessed the reliability of SMBG logs compared with glucometer memory in children with T1D and the impact on glycemic indicators. Children who maintained accurate records (aged 11.54 ± 4.05 years) had decreased HbA1c levels (from 10.79 ± 2.61% to 7.99 ± 0.84%) and those participants who kept inaccurate records had decreased HbA1c levels (from 10.74 ± 2.60% to 9.01 ± 2.33% over a period of 4 months (*p* < 0.002) [6]. There is a dearth of literature on testing of basic, cost-effective interventions to improve home-based and self-monitoring of blood glucose levels and management of insulin regimens with added beneficial lifestyle modifications. Therefore, the proposed study will record adherence to standard protocols for maintenance of SMBG records by patients, checking HbA1c level every three months, and maintaining an insulin dosage record on a daily basis to determine if these lead to reduction in acute complications in T1D patients, thereby reducing their illness-associated mortality and morbidity.

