### Outcome measures

The major outcome variable is HbA1c, measured at baseline and 3 and 6 months. HbA1C will be compared with the control (routine) group and with the other groups in this factorial design. This will also be compared within one group: baseline to 3 months and baseline to 6 months. We will explore between-group variation and within-group variation and any interactions between the groups over time.

In addition, secondary outcome variables will be number of all hypoglycemic episodes (blood glucose < 70 mg/dL (3.9 mmol/L) and ketoacidosis episodes (hyperglycemia blood glucose > 11 mmol/L, venous pH < 7.3, or serum bicarbonate < 15 mmol/L, ketonemia blood ß-hydroxybuyrate ≥ 3 mmol/L), taken as a composite variable at baseline and 3 and 6 months [30–32]. Total number of abnormal episodes counted over the follow-up period will be considered as a composite outcome.

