### Data analysis

We will use an intention-to-treat (ITT) analysis to evaluate changes in HbA1C and abnormal episodes of hypoglycemia and ketoacidosis. Generalized estimating equations will be used, with HbA1C readings at different points in time as our outcome variable. The mean change in HbA1C due to interventions will be estimated at 3 and 6 months, controlling for socio-demographic, clinical, nutritional, and physical activity variables. Secondary outcome variables are reported episodes of acute complications like hypoglycemia and diabetic ketoacidosis and will be recorded from interview-based data conducted at baseline and 3 and 6 months. In addition, these episodes will be further counted for the follow-up period using the daily log book of each participant.

Negative binomial regression will be used to observe the relationship among the four groups and number of episodes, adjusting for any socio-demographic, clinical, nutrition, and physical activity-related variables. If there is an excess number of ‘zeros’—meaning no abnormal episodes—then zero inflated negative binomial regression will be used instead of ordinary negative binomial regression. Twenty-four-hour dietary recall will be converted into total number of calories and percentage carbohydrate intake. Nutrition will be explored for total calories and food groups using factor analysis. Physical activity will be measured using step count data logged on a daily basis. These step counts will be used as time-dependent covariates for the final model. Step counts logged on a daily basis in two groups over a period of 6 months will be obtained from log books. The distribution of these data will be checked and, if needed, will be transformed. Changes in dietary habits and in step count over time will be used as a covariate in the final model. Physical activities reported during the three interviews will be converted into hours per week and categorized by type of activity as mild, moderate, and severe exercise.

In addition, we will explore blood glucose variability on a daily basis to calculate the average daily risk range for hypoglycemia using the standard method developed by Kovatchev and modified for relevant use by other investigators [15, 16].

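### The risk range and the log-based episode count rest on patient-entered glucose with no described check against meter memory, and the e-messages act on log keeping itself

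*Protocol article*

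**What the plan says.** **Recording.** The section on interventions covers every group: "A predesigned log book file will be provided to all patients in all groups to keep their records of daily blood sugar measurement and insulin". The abstract gives the collection route as: "Log book data will be obtained every 3 months electronically or during a patient’s clinic visit". The section on follow-up and other procedures gives the same 3-month interval: "Log book data will be obtained every 3 months during doctor visits or through e-messages".

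**Endpoints that use glucose values.**
- Glucose variability is a secondary objective. Data analysis says: "we will explore blood glucose variability on a daily basis to calculate the average daily risk range". No source is named there, and the log book is the only daily glucose record that the article describes.
- The episode outcome includes the "number of all hypoglycemic episodes (blood glucose < 70 mg/dL (3.9 mmol/L") and ketoacidosis, whose definition also uses laboratory criteria such as "venous pH < 7.3, or serum bicarbonate < 15 mmol/L" (Outcome measures).
- Data analysis says that episodes "will be recorded from interview-based data conducted at baseline and 3 and 6 months", and then that they are counted further over follow-up from each participant's log book. Data collection tools adds medical record files for extra clinic or hospital visits.

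**Evidence on log accuracy.** The Rationale reports: "A study done in India assessed the reliability of SMBG logs compared with glucometer memory in children with T1D". Some of those participants kept inaccurate records; the article gives no proportion.

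**What the messages target.** Randomization says that groups C and D are reminded about the log book, and group D also about glucose and steps. In Table 1 the messages for C ask for glucose checks and entries, while those for D concern steps and activity. The Discussion expects log keeping to rise substantially with messages.

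**The concern.** A secondary endpoint is compared fairly between randomised groups only if it is measured in the same way in each. Here one of the two randomised factors, the e-messages, acts on the measuring instrument. Randomisation balances the patients, but it does not balance an instrument that the intervention alters after allocation.

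Two mechanisms are possible, and they pull in different directions.
- Prompted patients may test and record more often, so more of their true lows enter the count. The message groups would then look worse on episodes.
- Prompted patients may smooth real readings or fill gaps with plausible values. Logged variability would then fall and the message groups would look better on it.

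Without an objective second record, neither mechanism can be detected or excluded. A difference in the risk range or in the log-based count, or the lack of one, could not be attributed to glucose.

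**Working it through.** The article states no figure that bears on this point, so there is none to reproduce. The check has three steps.

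**1. Which outcome depends on the log book?**

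| Outcome | Sources described | Dependence on log entries |
|---|---|---|
| HbA1c (primary) | Laboratory | None |
| Ketoacidosis episodes | Interview, medical records, laboratory criteria, log book | Partial |
| Hypoglycemic episodes | Interview, medical records for extra visits, log book | Substantial: a low outside the clinic is usually known only from what the patient logs or recalls |
| Average daily risk range | None named; the log book is the only daily glucose record | Whole |

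The article does not say how interview and log-book counts are combined.

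**2. Unequal completeness (illustration).** The documents give no capture rate, episode mean or dispersion, so all of these are assumptions. Let c be the share of true lows that reach the log. It is the chance of testing when low times the chance of writing the result down. With equal true rates:

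spurious rate ratio = c(prompted) / c(unprompted)

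For a Wald test on the log rate ratio with negative binomial counts, true mean m per patient, dispersion k and 30 patients per group (Sample size section):

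variance = (1/30) × [1/(m·c₁) + 1/k + 1/(m·c₂) + 1/k]; s = ln(c₂/c₁)/√variance; rejection = Φ(s − 1.96) + Φ(−s − 1.96)

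One case in full: m = 20, k = 1, c₁ = 0.5, c₂ = 0.7.
- Variance = (1.1000 + 1.0714)/30 = 0.0724, so SE = 0.269.
- ln(1.40) = 0.336, so s = 1.25.
- Rejection = 0.24.

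Over m = 10 to 40 and k = 1 to 2:

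| Capture without messages | Capture with messages | Spurious ratio | Rejection of a true null |
|---|---|---|---|
| 60% | 60% | 1.00 | 5% |
| 60% | 70% | 1.17 | 9% to 13% |
| 50% | 70% | 1.40 | 23% to 42% |
| 50% | 80% | 1.60 | 39% to 70% |
| 40% | 80% | 2.00 | 69% to 95% |

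These figures treat the count as coming from the log alone. Episodes found equally in all groups by interview or in medical records would pull the ratio towards 1, by an amount that cannot be derived from the article.

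**3. Unequal accuracy (direction only).** If a share f of entries is replaced by the patient's mean, the logged within-patient SD is multiplied by √(1 − f): √0.9 = 0.949 and √0.8 = 0.894, a fall of about 5% and 11%. This becomes a between-group bias only if f differs between groups, and the SD is not the risk range, so it shows a direction and not the size of bias in the planned endpoint.

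**The case against.** **Stronger readings that the documents do not support.**
- A reader might infer that every glucose-based secondary endpoint comes from a hand-written log. Episodes come first from interviews, medical records add to them, ketoacidosis uses laboratory values, and the article never says hand-written. Interviews are still self-report, so the dependence on the patient's account is reduced and not removed.
- A reader might infer that entries are less true in the prompted groups, or that the bias must favour the messages. Nothing in the article shows either. What it does expect is more log keeping, which would tend to count against the messages on episodes. Filling gaps also does not delete a recorded low; only suppressing or altering real readings would.
- A reader might use the HbA1c falls in the cited study as the size of the bias: 10.79 − 7.99 = 2.80 points in accurate recorders and 10.74 − 9.01 = 1.73 in inaccurate ones, a gap of 1.07. The accurate and inaccurate recorders were not randomised groups. The gap shows that accuracy went with better control, not how far log-derived endpoints err between arms.
- Groups C and D cannot be assumed equally prompted on glucose. The D messages in Table 1 concern steps, while Study design and Randomization say that D is also reminded about glucose.

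**Other defences.** Data management provides for phoning participants about missing or inappropriate information. That is again self-report and, if applied to log entries, could add recalled values. Table 2 collects frequency of self-monitoring and of log keeping at each visit. This helps with completeness but says nothing about accuracy. A condensed article may also leave source verification to the full protocol. That is fair, and a check may exist there; but the choice of the log book for the further episode count is stated here, beside a citation of the very check that is not described.

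**Conclusion.** The point holds for two secondary measures: the average daily risk range, which as described rests wholly on patient-entered values, and the log-based part of the episode count. Completeness of those entries can be expected to differ between groups, because the article itself predicts more log keeping under messages. A difference in accuracy is possible but not shown. The net direction of bias is unknown.

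The size cannot be fixed from the documents. Under assumed capture gaps from 60% against 70% up to 40% against 80%, the spurious ratio runs from 1.17 to 2.00, and the false-positive rate of a log-only comparison from about 9% to 95%. The width of that range reflects how little is known about capture.

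This should be corrected, but it does not threaten the main result: the laboratory HbA1c outcome does not pass through the log book.

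**What to change.** In all four groups:
1. Copy or photograph the glucometer memory at the scheduled 3- and 6-month visits, together with the log book.
2. Compute the risk range and the count of readings < 70 mg/dL from meter values over a common meter window where these exist, with the log book as fallback. Keep interviews, medical records and laboratory criteria as additional sources for episodes.
3. Report log-to-meter agreement and the number of readings by group.
4. Add a sensitivity analysis that accounts for the number of readings, for example lows per recorded reading. Meter data show whether entries are true, but they do not remove differences in how often patients test. Because testing frequency is itself affected by the messages, this analysis supports the main comparison and does not replace it.

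**Cost.** A short task for the data collector at visits already planned, with no new staff. Meter memory may not cover 3 months, some patients may lack a suitable meter, and some may send logs only by e-message. Eligibility already requires a smartphone in the patient's or a family member's hands, so a photograph of the memory could be requested by the same route. Where no meter record is obtained, report the number by group and label the endpoint as log-only.
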